**Study methods:** For this study subjects will be recruited for a targeted screening via pharmacies and general practitioners. For the pharmacies, subjects at risk of albuminuria will be identified as those with a prescription for Diabetes Mellitus, hypertension or lipid disorders. For general practitioners, subjects who have Diabetes Mellitus, cardiovascular disease, hypertension, lipid disorders, or obesity will be selected from electronic medical records. For the targeted screening, subjects are asked to collect urine at home for an albuminuria measurement. In case of elevated albuminuria, subjects will receive a second collection device for a confirmational measurement. If elevated albuminuria is confirmed, subjects will be invited for an elaborated screening visit. Elevated albuminuria will be defined as an urinary albumin creatinine ratio (UACR)  $\geq 3.0$  mg/mmol on two occasions in accordance with the prevailing primary care guideline ("NHG Standaard Chronische Nierschade"). If not confirmed, they will receive a third collection device. If the third collection device shows normal albuminuria, the study ends. In case of elevated albuminuria, subjects will be invited for an elaborated screening visit. During this screening visit, cardiovascular risk factors will be assessed, and medication use will be reviewed. A review report following the Dutch primary care guidelines will be provided to the subjects' general practitioner (GP). We aim to examine at least 112 patients with elevated albuminuria at the elaborated screening phase in this study. In the pilot, 57 patients with elevated albuminuria were screened in the elaborate screening phase. These patients were included from 2 pharmacies and 3 general practitioners. For the proposed extension, the pharmacies will be scaled up to a total of 5 and general practitioners to a total of 10. Six months after the study

visit, the frequency of cardiovascular monitoring and treatment changes via medication prescriptions will be monitored via data extraction of the general practitioners and/or pharmacies.

We assume that at least 6300 patients from general practices and pharmacies will be eligible for inclusion in the screening phase.

The costs of both screening approaches per identified patient with elevated albuminuria will be evaluated and compared.

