### 3 OBJECTIVES

#### 3.1 Primary objectives

To perform a study to:

1. Estimate the prevalence of elevated albuminuria in subjects with a high risk of chronic kidney disease in the Netherlands.
2. Evaluate which screening approach would be most effective based on costs per identified patient with elevated albuminuria, via pharmacies or general practices.

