## **5.4 Sample size calculation**

We aim to examine at least 112 patients with elevated albuminuria at the elaborated screening phase in this study. In the pilot study, 57 patients were examined at the elaborated screening phase. In the pilot study, 2 pharmacies and 3 general practitioners were included. For the extension, 3 pharmacies and 7 general practitioners will be recruited. We assume that at least 6300 patients from general practices and pharmacies will be eligible for inclusion in the screening phase.

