## **11 STATISTICAL ANALYSIS**

Characteristics of subjects recruited will be described as mean values with standard deviation or median with interquartile range for continuous variables. Categorical variables will be described as numbers and percentages of the subjects per category.

The overall prevalence of elevated albuminuria, and prevalences of unrecognized and persistent elevated albuminuria despite a RAS-inhibitor are described as percentages with 95% confidence intervals. The number of eligible patients from general practices who fulfilled the inclusion criteria but had an albuminuria level  $<3$  mg/mmol recorded within 18 months prior to selection (and where therefore not invited to participate), will be included in the denominator to calculate the prevalences.

To compare effectiveness and costs of screening on elevated albuminuria in pharmacies and in GP-care, the costs for the targeted screening strategies in both pharmacies and GPs will be calculated.

For each approach, all costs associated with the screening will be added and divided by the total number of subjects identified with confirmed elevated albuminuria. A screening-

approach will be considered more effective than the other if the costs per identified patient are  $\geq 10\%$  lower.

Frequencies of cardiovascular monitoring and treatment changes are summarized as numbers and percentages with 95% confidence intervals.

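### The 10% cost rule for primary objective 2 compares point estimates with no allowance for sampling error, so it can often name a better screening route when neither is better

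*Protocol*

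**What the plan says.** The comparison of routes is a primary objective. Protocol section 3.1 sets out to "Evaluate which screening approach would be most effective based on costs per identified patient with elevated albuminuria, via pharmacies or general practices".

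Section 11 fixes the estimator. For each route, "all costs associated with the screening will be added and divided by the total number of subjects identified with confirmed elevated albuminuria". It also fixes the decision: a route's "approach will be considered more effective than the other if the costs per identified patient are" at least 10% lower than the other's. Section 11 plans 95% confidence intervals for the prevalences and for the monitoring and treatment frequencies. The cost rule refers to no interval.

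The only case target is in section 5.4: "We aim to examine at least 112 patients with elevated albuminuria at the elaborated screening phase in this study". It is not divided by route. The same section adds that "In the pilot study, 57 patients were examined at the elaborated screening phase". On sites, the Summary says that "the pharmacies will be scaled up to a total of 5 and general practitioners to a total of 10". Table 1 in section 9.1.1 lists the cost items but gives no amounts.

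**The concern.** Cost per identified patient is a total divided by a count, and the count varies by chance. With perhaps 40 to 75 cases in a route, that variation is large against a 10% margin. A rule that reads the margin straight off the two point estimates will therefore sometimes declare a winner between equal routes, and sometimes declare the dearer one.

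The result is meant to be used. Under its novel aspects, the Summary says the study will guide later, larger programmes. Section 4 foresees a possible amendment, based on the results, to extend screening to a larger population. A conclusion that one route is more effective would carry weight in both.

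**Working it through.** **The plan's own figure.** The target of 112 comes with no error rate, power, effect size or precision, so no formula can reproduce it. No error rate is stated for the 10% rule either. What follows is the rule's behaviour under stated assumptions.

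**Inputs from the protocol**
- Rule: declare a winner if the estimated cost ratio is ≤ 0.90 or ≥ 1/0.90 (section 11). On the log scale the margin is −ln 0.90 = 0.1054.
- Cases: at least 112 examined at the elaborated visit (section 5.4), used as the low value for confirmed cases.
- Sites: 5 pharmacies and 10 practices (Summary, study methods).

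**Assumptions**
- Poisson case counts and route costs that do not depend on the number of cases found.
- A split of cases by route of 1:1 to 1:2.
- Totals of 112, 171, 300 and 400 confirmed cases. The 171 is the pilot yield scaled from 5 to 15 sites: 57 × 15/5. If the 112 is additional to the pilot's 57, the total is 169, practically the same.

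**Formulas.** With expected cases a and b, SE(log ratio) = √(1/a + 1/b). If the true costs per case are equal, P(winner declared) = 2 × [1 − Φ(0.1054/SE)].

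| Confirmed cases | Split | SE | P(winner, routes equal) |
|---|---|---|---|
| 112 | 56 : 56 | 0.189 | 58% |
| 112 | 37.3 : 74.7 | 0.200 | 60% |
| 171 | 85.5 : 85.5 | 0.153 | 49% |
| 171 | 57 : 114 | 0.162 | 52% |
| 300 | 1:1 to 1:2 | 0.115 to 0.122 | 36–39% |
| 400 | 1:1 to 1:2 | 0.100 to 0.106 | 29–32% |

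For 56 : 56, 0.1054/0.189 = 0.56, so the margin is just over half a standard error. Exact Poisson enumeration agrees (58.2% and 60.5% at 112; 49.5% and 52.0% at 171).

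**Relaxing the assumptions**
- If 10–30% of cost rises in proportion to cases, the figure at 112 cases falls to between 56% and 43% (simulation).
- With a between-site coefficient of variation in yield of 0.2–0.3 (assumed) and a 1:2 split, it rises to 65–69% at 112 cases and 60–65% at 171 (simulation).

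**Naming the wrong route.** If one route is truly 10% dearer, it is called the better one with probability Φ[−(0.1054 + ln 1.1)/SE]. With 112 cases split evenly this is Φ(−0.2007/0.189) = Φ(−1.06), about 14%.

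**What the data can resolve.** With SE 0.189, a 95% interval multiplies and divides the ratio by exp(1.96 × 0.189) = 1.45. It excludes 1 only for observed ratios below about 0.69 or above about 1.45. Keeping the unaided 10% rule to 5% false declarations would need 4 × (1.96/0.1054)² ≈ 1,385 cases at 1:1, or about 1,560 at 1:2.

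**The case against.** Four points can be made for the plan.

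First, 112 is not the rule's denominator. It is a minimum for patients examined at the visit, whereas the rule counts everyone with confirmed elevated albuminuria. Not everyone confirmed need attend, so confirmed cases may be more numerous, and the error rate falls as they increase. This stands. A reader might infer that the rule declares a false winner in a fixed 50–60% of studies, or that it will usually name one. The protocol supports neither: it gives no attendance rate, no split and no cost amounts. The figure has to be a conditional range.

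Second, the costs are not all fixed. Table 1 includes collection devices and laboratory work, and section 4.1 sends confirmatory devices only after a positive result. This stands, and the range allows for it.

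Third, 10% can be read as a materiality threshold in a descriptive, non-randomised study that claims no significance level. The two routes also select people differently, so exact equality is unlikely. That is fair: the rule does better when the routes differ widely. At a true ratio of 0.70 and 112 cases it picks the cheaper route in about 90% of studies. But section 11 does not label the threshold descriptive. It draws a conclusion of greater effectiveness from it.

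Fourth, a statistical analysis plan may add an interval. A reader might take the missing interval as the defect. It is not, because that detail can be left to a later plan. The defect is the rule the protocol has already fixed: an added interval would not alter the conclusion while that sentence stands.

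**Conclusion.** The point holds in conditional form. Section 11 decides a primary objective on two point estimates and a fixed 10% cut, with no allowance for chance in the case counts. Depending on inputs the protocol does not give, equal routes would yield a declared winner in roughly 30% to 70% of studies. The low end needs about 400 confirmed cases; the high end combines 112 cases with moderate variation between sites. Poisson counts, the split by route, the cost structure and the between-site variation are all assumptions. None of the settings examined comes near a conventional error rate.

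This should be fixed before the analysis. It is not more serious than that: no participant is affected, no data are lost, and any further extension would still go through an amendment put forward for ethical approval.

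**What to change.** Amend section 11 to report the pharmacy/GP ratio of cost per identified patient with a 95% confidence interval that allows for clustering by site. Then choose one of two conclusion rules:

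1. Call a route more effective only if its cost per identified patient is at least 10% lower and the interval excludes 1; otherwise conclude that no difference was shown.
2. Keep 10% as a descriptive materiality threshold, and draw no conclusion of greater effectiveness from the point estimate alone.

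The plan should say that a bootstrap over 5 pharmacies and 10 practices is approximate and may be too narrow. In simulations of equal routes with Poisson counts, resampling sites only, the nominal 95% interval excluded 1 in about 8–13% of runs instead of 5%.

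The cost is a changed rule and one further analysis of data already being collected. The price of option 1 is more inconclusive results: at an SE of 0.19 only observed ratios below about 0.69 or above about 1.45 would be conclusive, so the 10% margin would rarely bind. Option 2 avoids that, but gives up a formal choice between the routes.

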#### Evaluating non-response:

Aggregated data of characteristics from the total population of subjects that is eligible for screening will be collected from each general practice through VIPLive and will be combined to describe pooled characteristics of the total eligible population from general practices (Table 2).

*Table 2. Distribution of characteristics of the study population selected from participating general practices*

| Characteristic                         | Distribution              |
|----------------------------------------|---------------------------|
| Age                                    | Mean (standard deviation) |
| Sex, female                            | Number (%)                |
| Diabetes Mellitus                      | Number (%)                |
| Elevated albuminuria in last 11 months | Number (%)                |
| Lipid disorder                         | Number (%)                |
| Obesity                                | Number (%)                |
| Hypertension                           | Number (%)                |
| Cardiovascular disease                 | Number (%)                |
| Kidney disease                         | Number (%)                |

Pharmacies will be asked to provide similar data used to select their subjects.

The distribution of subject characteristics in the total selected population will be compared with the distribution among responders using collected information to evaluate occurrence of systematic response bias. Collected information of responders will be used for post-stratification and weighting methods to account for potential response bias in the estimation of prevalences (19).

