#### Albuminuria screening using PeeSpot

Selected subjects will receive an invitation to participate in the screening survey from their pharmacy or general practice by postal mail, including an informational letter about the study, an informed consent form, a short questionnaire to be completed (Appendix 16.1)

and a urine collection device (PeeSpot) with instructions. The participant will be asked to send the signed informed consent form and completed questionnaire and the collected urine to the General Practitioners Research Institute (GPRI) by postal mail (without costs). If the laboratory measures 'normal' albuminuria ( $<3.0$  mg/mmol), GPRI will inform the subject. In case of elevated albuminuria ( $\geq 3.0$  mg/mmol), GPRI will be informed to send a second PeeSpot for a confirmational measurement if informed consent has been received. If this second measurement is also elevated ( $\geq 3.0$  mg/mmol), subjects will be invited for an elaborated screening visit performed by GPRI (phase 2). A second confirmational measurement of elevated albuminuria will not be required when a recent (within 11 months) measurement performed by the general practice also indicated elevated albuminuria.

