#### **4.2 Phase 2: Elaborated screening phase**

When there is no elevated albuminuria at phase 1, a letter with the results will be sent to the participant, and no further actions from the participant are required. Subjects will be carefully informed about the results.

When elevated albuminuria is confirmed ( $\geq 3.0$  mg/mmol on two occasions), subjects are invited for an elaborated screening visit with a researcher. At the start of the visit, participants will be asked to provide informed consent. Next, CKD/CVD risk factors will be assessed and the participant's medication use, and medication adherence will be reviewed during an interview. GPRI will produce a report of their findings which will be shared with the general practice, including recommendations for additional measurements or treatment changes if applicable.

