## 9 METHODS

### 9.1 Study endpoints

#### 9.1.1 Primary endpoints

1. Elevated albuminuria, defined as a urinary albumin creatinine ratio (UACR)  $\geq 3.0$  mg/mmol.
2. Average screening costs per subject that was identified as having kidney disease by screening for albuminuria. All costs considered are mentioned below (Table 1)

Table 1. Costs associated with screening

|                                                                             |
|-----------------------------------------------------------------------------|
| Costs of the PeeSpot                                                        |
| Laboratory costs                                                            |
| Printing and postal mailing costs of all invitations and needed information |
| Labor costs needed to recruit and start GP's and pharmacies                 |
| Labor costs of training GP's and pharmacies                                 |
| Costs of extracting patients eligible for inclusion                         |

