#### **9.4 Withdrawal and replacement of individual subjects**

Subjects can leave the study at any time for any reason if they wish to do so without any consequences. The investigator can decide to withdraw a subject from the study. There are no specific criteria for withdrawal. Every subject that meets the inclusion criteria is invited, therefore replacement is not possible.

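### Subjects lost between an elevated first PeeSpot and its confirmation can distort the confirmed prevalence, and the planned response weighting cannot correct this

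*Protocol*

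**What the plan says.** The Summary (Study methods) defines elevated albuminuria as a UACR of at least 3.0 mg/mmol "on two occasions in accordance with the prevailing primary care guideline". Section 4.2 also speaks of two occasions. The endpoint list is shorter: section 9.1.1, like the endpoint list in the Summary, reads "Elevated albuminuria, defined as a urinary albumin creatinine ratio (UACR" and goes on to the 3.0 mg/mmol threshold without mentioning a second measurement.

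The confirmation sequence runs by post. After an elevated first result (section 4.1), "GPRI will be informed to send a second PeeSpot for a confirmational measurement if informed consent has been received". The Summary adds: "If not confirmed, they will receive a third collection device". There is one exemption in section 4.1: "A second confirmational measurement of elevated albuminuria will not be required when a recent (within 11 months) measurement performed by the general practice" was elevated as well. A normal first result ends the sequence.

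Section 9.4 lets subjects leave at any time and rules out replacement.

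Section 11 gives prevalences as percentages with 95% confidence intervals. It adds to the denominator the practice patients who were not invited because of a recent normal value. For non-response it compares the selected population with responders on the characteristics used for selection (Table 2), and then: "Collected information of responders will be used for post-stratification and weighting methods to account for potential response bias in the estimation of prevalences". Table 2 does not contain the study's first UACR.

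**The concern.** Case finding is sequential, and only one branch can remain unfinished. Among subjects who return the first kit, an open outcome can occur only after an elevated result, so missingness is tied to the outcome being estimated. Weights built on age, sex and risk factors restore the mix of the selected population. They do not restore the first-positives who never completed confirmation.

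At stake is the first primary endpoint. The secondary prevalences of unrecognised and persistent elevated albuminuria rest on the same classification. A larger sample would not help. The cost endpoint is less affected, since section 11 divides costs by confirmed cases and a subject who never completes confirmation has not been identified.

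**Working it through.** **Plan's own figure.** There is none to reproduce. The protocol gives a target of 112 examined patients and at least 6,300 eligible, but no expected prevalence, response rate, confirmation rate or second-kit return rate. All rates below are assumptions.

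**Notation.** f = share of responders with an elevated first kit; c = share of these who would be confirmed; d = share of first-positives lost before confirmation, unrelated to true status. The target is f·c.

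- Lost counted as non-cases: f·c·(1−d); relative bias −d.
- Lost dropped: f·c·(1−d)/(1−f·d).
- Lost counted as cases: f·c·(1−d) + f·d.

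**Example.** f = 13%, f·c = 10%.

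| d | Non-cases | Dropped | Cases |
|---|---|---|---|
| 10% | 9.0% | 9.0/0.987 = 9.1% | 9.0 + 1.3 = 10.3% |
| 20% | 8.0% | 8.0/0.974 = 8.2% | 8.0 + 2.6 = 10.6% |
| 30% | 7.0% | 7.0/0.961 = 7.3% | 7.0 + 3.9 = 10.9% |

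With an assumed 2,000 responders and d = 20%, the simple interval around 8.0% is 0.08 ± 1.96·√(0.08·0.92/2000) = 6.8% to 9.2%, which misses 10%. This illustration leaves out the weights and the added uninvited patients.

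**Range.** For f 10–30%, c 50–90% and d 5–30%, the relative bias is −5% to −30% (non-cases), −3.6% to −27.8% (dropped) and +0.6% to +30% (cases).

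**Does weighting help?** Assume 30% have diabetes; first kit elevated in 30% with diabetes and 15% without; first-kit response 50% and 35%; c = 70%; d = 20%. After exact weighting on diabetes the response rates cancel, so f = 0.30·0.30 + 0.70·0.15 = 19.5% and the target is 0.195·0.70 = 13.65%.

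- Lost as non-cases: 13.65·0.8 = 10.92%.
- Lost dropped: 10.92/(1 − 0.195·0.2) = 11.36%.
- Only completers treated as responders, then post-stratified: 0.30·(0.168/0.94) + 0.70·(0.084/0.97) = 11.42%.

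A simulation of 2,000,000 subjects agrees within 0.1 percentage point. The weights leave the loss in place on either reading of responders.

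**Exemption.** If a share e of first-positives is exempt and counted as confirmed, and d applies to the rest, the relative bias with lost as non-cases is −d·(1−e)c/[e + (1−e)c]. This is smaller in size than d, and is why the loss rate is an upper limit here.

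**Loss related to true status.** With f = 20%, c = 70% (true 14.0%) and loss of 0% in confirmers and 30% in non-confirmers, counting the lost as non-cases gives 14.0% and dropping them gives 14.0/0.982 = 14.3%. With 30% and 10% instead, the figures are 9.8% and 10.3%.

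**Two-stage estimate.** At f = 13% and d = 20%: 13% × (8.0/10.4) = 10.0%, the target. In the case with loss only in non-confirmers it gives 20% × 14.0/(14.0 + 4.2) = 15.4%, which is too high, while the none/all bounds are 14.0% and 14.0 + 1.8 = 15.8%. The bounds are therefore needed beside it.

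**The case against.** A reader might infer that the primary prevalence is biased low. The documents do not support that as stated. On the literal wording of section 9.1.1 a single elevated UACR is enough, and loss after the first kit then causes no bias. Even for a confirmed endpoint the sign depends on how unconfirmed subjects are classed, which the protocol does not fix. This part of the objection stands.

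A reader might also infer that investigators will remove subjects once a positive result is known, because section 9.4 says: "The investigator can decide to withdraw a subject from the study. There are no specific criteria for withdrawal". That is a general clause and says nothing about timing or results. Nor does section 9.6 show that results are discarded: it concerns withdrawal from treatment, and section 6 says there is no treatment. Ordinary failure to return a kit is enough for the mechanism.

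It is fair to add that responders are not defined in section 11, that exempt subjects are not exposed, that every size above is assumed, and that detailed missing-data rules may sit in an analysis plan not shown here. The last point does not remove the concern. The protocol itself fixes a denominator rule and names a correction for the prevalences. The criticism is that this correction acts on first-stage response only, which further detail about those weights would not change.

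**Conclusion.** The concern holds in a conditional form. For a confirmed endpoint, unfinished outcomes among first-kit returners fall only on non-exempt first-positives, and weighting on selection characteristics cannot correct them. If the unconfirmed are counted as non-cases, the relative understatement equals the loss rate when loss is unrelated to true status and nobody is exempt, and is smaller with exemptions. If they are dropped, the estimate is generally low, though it can be slightly high when almost all of those lost would not have been confirmed. If they are counted as cases, it is high. The actual size cannot be derived from the protocol. The mismatch between the single-measurement wording in section 9.1.1 and the two-occasion definition in the Summary and section 4.2 has to be settled first, because it decides whether the problem arises at all.

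**What to change.** 1. In sections 9.1.1 and 11, and in the Summary's endpoint list, state that the primary prevalence is of confirmed elevated albuminuria, in line with the Summary's study methods and section 4.2.
2. In section 11, estimate it as f × [e + (1−e)·c]. Here f is the weighted share with an elevated first PeeSpot, with the uninvited patients kept in the denominator as already planned. The share e is the exempt first-positives, counted as confirmed. The share c is those confirmed among non-exempt first-positives who completed the sequence, weighted by first UACR and recruitment route. Only subjects with a normal second result face the third kit, so if losses occur there the weights should also use the second result.
3. Let the confidence interval cover both stages, for example by bootstrapping them together.
4. Report bounds with none and with all of the unconfirmed first-positives as cases. The two-stage figure still assumes that loss is unrelated to true status given the weighting variables.
5. Report, per route, the number lost between the first and the confirmatory kit.

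The cost is some protocol wording, a little extra analysis and a slightly wider interval. No new data are needed: the UACR results and the recruitment route are already recorded.
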